### 3.3. Sample Size

The sample size was calculated on the basis of previous studies. In the PARTNER cohort B trial, the patients were not considered to be suitable candidates for surgery after evaluation by a cardiologist and two cardiovascular surgeons. Patients that did not have significant comorbidities were enrolled as having prohibitive surgical risk if their STS score was 10% or higher. In this trial, the 30-day all-cause mortality in TAVI patients with prohibitive surgical risk (n = 179) was 5% [7]. In PARTNER cohort A, including 348 high-surgical-risk patients treated with TAVI, the rate of death from any cause was 3.4% at 30 days [8].

In the national US registry, 7710 patients were enrolled, including 1559 (20%) inoperable patients and 6151 (80%) with high-risk cases. Among the 3133 patients for whom 30-day outcome data were available, the incidence of death was 7.6% [29].

In an analysis of the prospective Austrian TAVI registry, 30-day mortality in high-risk and inoperable patients undergoing transfemoral TAVI was 6.2% in patients treated in hospitals with CS on site [30]. Unfortunately, updated 30-day mortality data for patients with prohibitive or high surgical risk are not available. The available literature data are summarized in Table 3.

According to these data, the mean 30-day mortality rate is 6.6%. The sample size will be 200 patients, which demonstrates the non-inferiority of the alternative treatment strategy compared to the standard of care with an alpha error of 5%. We considered a non-inferiority margin of 3%, such as to exclude mortality rates greater than 10% at the upper limit of the 90% confidence interval.

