### 3.4. Data Analysis

All of the variables will be described through descriptive statistics: absolute frequencies and percentages for the qualitative and categorical variables, mean and standard deviation for the quantitative variables with normal distribution, and median and interquartile range for the ordinal or quantitative variables with non-normal distribution. For all parameters, 95% confidence intervals will be calculated. Kaplan–Meier curves, the log-rank test, and Cox regression will be performed and used to identify prognostic factors associated with survival. Other parametric (Student’s *t*-test) and non-parametric (chi-square test and Mann–Whitney tests) statistical tests will be used to study the relationship between patient characteristics and secondary endpoints. The significance threshold used for all tests will be 0.05. All analyses will be performed using STATA software, version 17.0.

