### 3.5. Outcome Measures

The primary endpoint will be 30-day all-cause mortality, which will be measured as the number of deaths within 30 days of the procedure. Secondary endpoints will include the assessment of technical success and the evaluation of single complications at 30 days after the procedure [32]. Technical success will be defined according to VARC-3 consensus [32]:-Freedom from mortality.-Successful access, delivery of devices, and retrieval of the delivery system.-Correct positioning of a single prosthetic heart valve into the proper anatomical location.-Freedom from surgery or intervention related to the device (excluding pacemaker implantation) or to a major vascular, access-related, or cardiac structural complication.

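### The 3-point margin on the 6.6% reference gives a ceiling of 9.6%, not the printed 10%; the reference rate, margin and ceiling need to be reconciled together

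*Protocol article*

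**What the plan says.** All the elements of the primary criterion are in section 3.3 (Sample Size) of the protocol article.

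- Reference rate: "According to these data, the mean 30-day mortality rate is 6.6" per cent.
- Margin and limit: "We considered a non-inferiority margin of 3%, such as to exclude mortality rates greater than 10" per cent. The limit is applied to a 90% interval: "exclude mortality rates greater than 10% at the upper limit of the 90% confidence interval".
- Size and error rate: "The sample size will be 200 patients, which demonstrates the non-inferiority of the alternative treatment strategy compared to the standard of care". The same sentence sets alpha at 5%.

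The endpoint (section 3.5) is a simple count: "The primary endpoint will be 30-day all-cause mortality, which will be measured as the number of deaths within 30 days of the procedure".

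The reference rate comes from the four cohorts in Table 3. For the Austrian registry, Table 3 prints 2/290 beside 6.9%, while the text of section 3.3 says "30-day mortality in high-risk and inoperable patients undergoing transfemoral TAVI was 6.2% in patients treated in hospitals with CS on site".

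**The concern.** The sentence presents the 10% limit as the result of applying a 3% margin, but the printed figures do not produce it: 6.6% plus 3 points is 9.6%. A reader who applies the margin tests against 9.6%; a reader who applies the printed limit tests against 10%.

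The study has one arm, so this fixed limit carries the whole non-inferiority conclusion. The gap of 0.4 points would be harmless if no possible result fell inside it. The expected number of deaths at 6.6% is 200 × 0.066 = 13.2, and upper limits for 13 and 14 deaths lie close to 10%. If the ceiling were chosen after the count is known, that choice could decide the conclusion.

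**Working it through.** **Inputs.** n = 200, reference 6.6%, margin 3 points, printed limit 10%, 90% interval (all section 3.3); cohort counts (Table 3).

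**1. Reproduce the reference rate.** Deaths 9 + 12 + 239 + 2 = 262. Patients 179 + 348 + 3133 + 290 = 3950. 262/3950 = 6.63%, the plan's 6.6%. So the figure is the pooled rate, and it uses the printed 2/290.

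**2. Margin against limit.** 6.6% + 3.0% = 9.6%. 10% − 6.6% = 3.4 points.

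**3. Check the Austrian entry.** 2/290 = 0.69%, which matches neither stated rate. 20/290 = 6.90% (Table 3) and 18/290 = 6.21% (text). The counts 20 and 18 are inferred from those percentages; the document does not print them.

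- With 20: 280/3950 = 7.09%; plus 3 points = 10.09%.
- With 18: 278/3950 = 7.04%; plus 3 points = 10.04%.

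Either correction brings margin and limit into agreement at about 10%.

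**4. Upper 90% limits for x deaths in 200** (p = x/200, z = 1.645). Wald: p + z√(p(1−p)/200). Wilson: the score limit. Jeffreys: 95th percentile of Beta(x + 0.5, 200 − x + 0.5). Clopper-Pearson: 95th percentile of Beta(x + 1, 200 − x).

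| Deaths | Wald | Jeffreys | Wilson | Clopper-Pearson |
|---|---|---|---|---|
| 12 | 8.76% | 9.24% | 9.39% | 9.54% |
| 13 | 9.37% | 9.84% | 9.99% | 10.14% |
| 14 | 9.97% | 10.43% | 10.58% | 10.73% |

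Reading down one column at a time, the choice of 9.6% or 10% matters at:

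- Wald: 14 deaths
- Jeffreys and Wilson: 13 deaths
- Clopper-Pearson: no count (12 passes both limits, 13 fails both)

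**5. How likely those counts are.** Binomial(200, 0.066): P(X = 13) = 11.35%, P(X = 14) = 10.71%.

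**6. Operating characteristics of each cut-off** (exact binomial, P(X ≤ cut-off)).

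| Pass if deaths ≤ | True 6.6% | True 7.0% | True 9.6% | True 10% |
|---|---|---|---|---|
| 12 | 43.7% | 35.1% | 4.7% | 3.2% |
| 13 | 55.0% | 46.1% | 8.0% | 5.7% |
| 14 | 65.7% | 57.0% | 12.7% | 9.3% |

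The last two columns are the one-sided type I error if the ceiling is 9.6% or 10%.

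**7. Does n = 200 show which ceiling was meant?** Wald precision, n = z²p(1−p)/d²: with p = 6.6%, d = 3 points gives 186 and d = 3.4 points gives 145. Neither is 200. With the corrected 7.04% or 7.09% and d = 3 points, n is 197 or 198. No power is stated, so this is suggestive only.

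**The case against.** The strongest reply is that the article prints only one ceiling, 10%. The figure 9.6% appears nowhere, and 10% may be a rounding of it, in which case 10% is the operational limit and the fault is loose arithmetic. This stands in part. It is wrong to say that the plan states two rival limits; one is printed and one is implied. But the sentence derives the limit from the margin, both inputs are printed, and under common interval methods a possible result falls in the gap.

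A reader might go further in three ways that the document does not support.

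- **That leaving the interval method unnamed is itself an error.** A condensed article may leave this to an analysis plan that is not shown. For the same reason, the 22% probability of 13 or 14 deaths (11.35% + 10.71%) overstates the point, because it lets both ceiling and method vary.
- **That the plan's rule runs at 8.0% or 9.3% type I error instead of 5%.** Those are the figures for Wald cut-offs of 13 deaths at 9.6% and 14 deaths at 10%. The document never names Wald.
- **That n = 200 shows 9.6% was intended.** The stated inputs give 186, and the expected Wald limit at 6.6%, 9.49%, lies below both ceilings.

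**Conclusion.** The point holds in a limited form. As printed, the 6.6% reference, the 3% margin and the 10% limit cannot all be right. With the method fixed, the inconsistency affects a single death count, with a probability of about 11% at a true 6.6% under Wald, Wilson or Jeffreys, and none under Clopper-Pearson.

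The mismatch is probably a consequence of the Austrian entry in Table 3, since correcting that count to either stated rate moves reference plus margin to about 10%. This attribution rests on inferred counts of 18 or 20. The probabilities assume n = 200 evaluable patients and independent binomial deaths. Because this is the only success threshold in a study without a control arm, it should be settled before results are known.

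**What to change.** In section 3.3 and Table 3:

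1. Check the Austrian registry count against its source, make text and table agree, and recompute the pooled reference rate.
2. State one ceiling, equal to that rate plus the margin, and remove the other.
3. Give the primary criterion as a maximum number of deaths out of 200, from a named two-sided 90% interval.

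One workable rule is Clopper-Pearson with at most 12 deaths (upper limit 9.54%). It satisfies both 9.6% and 10%, and keeps one-sided type I error at 4.7% and 3.2% respectively. It would also be unchanged by a corrected ceiling of 10.04% or 10.09%, because 13 deaths gives 10.14%. Other methods are defensible if named in advance.

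The edit is short, but its cost must be disclosed. The 12-death rule is met about 44% of the time at a true 6.6% and 35% at a true 7.0%, against 55% or 66% at 6.6% for cut-offs of 13 or 14. At the planning rate, 200 patients would be more likely to fail this rule than to meet it. The sponsor should either accept and state that, or revisit the sample size.

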### 3.4. Data Analysis

All of the variables will be described through descriptive statistics: absolute frequencies and percentages for the qualitative and categorical variables, mean and standard deviation for the quantitative variables with normal distribution, and median and interquartile range for the ordinal or quantitative variables with non-normal distribution. For all parameters, 95% confidence intervals will be calculated. Kaplan–Meier curves, the log-rank test, and Cox regression will be performed and used to identify prognostic factors associated with survival. Other parametric (Student’s *t*-test) and non-parametric (chi-square test and Mann–Whitney tests) statistical tests will be used to study the relationship between patient characteristics and secondary endpoints. The significance threshold used for all tests will be 0.05. All analyses will be performed using STATA software, version 17.0.

### 3.5. Outcome Measures

The primary endpoint will be 30-day all-cause mortality, which will be measured as the number of deaths within 30 days of the procedure. Secondary endpoints will include the assessment of technical success and the evaluation of single complications at 30 days after the procedure [32]. Technical success will be defined according to VARC-3 consensus [32]:-Freedom from mortality.-Successful access, delivery of devices, and retrieval of the delivery system.-Correct positioning of a single prosthetic heart valve into the proper anatomical location.-Freedom from surgery or intervention related to the device (excluding pacemaker implantation) or to a major vascular, access-related, or cardiac structural complication.

## 4. Conclusions

The aim of this study is to evaluate an innovative treatment strategy for patients with severe AS and indications for TAVI. The results are expected to provide prospective evidence on the efficacy and safety of TAVI performed in centers without on-site CS. In addition, extending TAVI procedures to centers without CS could represent a solution to reduce waiting times and ensure continuity of care, particularly for elderly and frail patients, for whom emergency cardiac surgery in the case of severe complications may be futile.

## Figures and Tables

**Figure 1 jcdd-12-00063-f001:**
[figure not shown]
Study scheme.

**Table 1 jcdd-12-00063-t001:** Conversion to emergent cardiac surgery and principal structural complications after TAVI in principal international registries [14,21,22,23,24]. # 30-day mortality; * in-hospital mortality; ^ 24 h mortality.

	Source (2007–2009)	Source 3 (2014–2015)	France 2 (2010–2012)	France (2013–2015)	Gary (2010–2015)	STS (2011–2019)
N.° of patients	1038	1947	4165	12,557	15,964	276,316
Mean age	81	81	83	83	81	81
LogES (%)	27	18	22	18	18	-
Death (%)	8.5 #	2.2 #	8.1 *	4.4 *	1 ^/5.2 *	2.0 */3.1 #
Conversion to open surgery (%)	2.7	0.6	1.2	0.5	1.3	0.6
Ring rapture (%)	-	0.2	0.3	0.4	0.4	-
Aortic dissection (%)	-	-	0.2	0.4	0.2	-
Coronary obstruction (%)	-	0.4	-	-	-	-
Cardiac tamponade (%)	-	-	1.3	2	1.0	-
Valve malposition (%)	0.3	-	1.3	1.1	-	-
2° Valve implantation (%)	-	0.7	2.3	1.8	-	-

**Table 2 jcdd-12-00063-t002:** Eligibility criteria.

Inclusion criteria - Severe symptomatic aortic valve stenosis - Age ≥ 75 years - Patients evaluated by Heart Team and selected on the basis of at least one of the following criteria: 1. High surgical risk (LogES > 20%, EuroSCORE II > 8%, and STS score > 8%) 2. Porcelain aorta 3. Hostile chest 4. Severe fragility 5. Severe liver disease/cirrhosis 6. Presence of a patent graft of an internal mammary artery crossing midline and/or adherent to the posterior table of the sternum 7. Severe pulmonary hypertension or severe right ventricular dysfunction - Feasible transfemoral access - Signed informed consent form
Exclusion criteria - Aortic valve bioprosthetic dysfunction - Bicuspid aortic valve - Anatomical features associated with an increased risk of major complications: 1. Severe left ventricle outflow tract or sub-annular calcification 2. Valvular ring to coronary ostia distance < 10 mm 3. Severe aortic root dilatation or out-of-range aortic annulus diameters for TAVI - Contraindication for femoral access

**Table 3 jcdd-12-00063-t003:** Thirty-day all-cause mortality after TAVI in patients with high or prohibitive surgical risk [7,8,29,30].

	Partner Trial		STS/ACCTVT Registry	Austrian Registry
	Inoperable	High-Risk	Inoperable + High-Risk	Inoperable + High-Risk
30 Days	(9/179) 5.0%	(12/348) 3.4%	(239/3133) 7.6%	(2/290) 6.9%

## Data Availability

No new data will be created or analyzed for this article and data sharing will not be applicable. The raw data that will be generated in the course of the clinical study will be made available by the authors upon request.

## Abbreviations

Aortic stenosis (AS); cardiac surgery (CS); Heart Team (HT); transcatheter aortic valve implantation (TAVI); surgical aortic valve replacement (SAVR); United States (US).
